## Abstract

**Background:**

For residential aged care facility (RACF) residents with dementia, lack of prognostic guidance presents a significant challenge for end of life care planning. In an attempt to address this issue, models have been developed to assess mortality risk for people with advanced dementia, predominantly using long-term care minimum data set (MDS) information from the USA. A limitation of these models is that the information contained within the MDS used for model development was not collected for the purpose of identifying prognostic factors. The models developed using MDS data have had relatively modest ability to discriminate mortality risk and are difficult to apply outside the MDS setting. This study will aim to develop a model to estimate 6- and 12-month mortality risk for people with dementia from prognostic indicators recorded during usual clinical care provided in RACFs in Australia.

**Methods:**

A secondary analysis will be conducted for a cohort of people with dementia from RACFs participating in a cluster-randomized trial of a palliative care education intervention (IMPETUS-D). Ten prognostic indicator variables were identified based on a literature review of clinical features associated with increased mortality for people with dementia living in RACFs. Variables will be extracted from RACF files at baseline and mortality measured at 6 and 12 months after baseline data collection. A multivariable logistic regression model will be developed for 6- and 12-month mortality outcome measures using backwards elimination with a fractional polynomial approach for continuous variables. Internal validation will be undertaken using bootstrapping methods. Discrimination of the model for 6- and 12-month mortality will be presented as receiver operating curves with c statistics. Calibration curves will be presented comparing observed and predicted event rates for each decile of risk as well as flexible calibration curves derived using loess-based functions.

**Discussion:**

The model developed in this study aims to improve clinical assessment of mortality risk for people with dementia living in RACFs in Australia. Further external validation in different populations will be required before the model could be developed into a tool to assist with clinical decision-making in the future.

## Background

Health professionals working in residential aged care facilities (RACFs) providing long-term care play a key role in end of life care decision-making for residents with dementia. Uncertainty regarding prognosis and difficulty identifying people with dementia whose health is deteriorating presents a significant barrier to initiating discussions of a palliative approach to care [1, 2]. In countries such as the USA, assessment of estimated life expectancy is a central consideration in determining who can access palliative care services such as hospice care [3] but health professionals often do not feel confident making prognostic assessments for people with dementia [4].

Planning for end of life care is infrequently discussed in the months prior to death for people with dementia living in RACFs [5] and emergency services are increasingly utilized toward the end of life [6]. In order to improve the quality of end of life care, timely recognition of end of life illness trajectory is essential to support carers and health care proxy decision-makers (usually the closest family member or a formally appointed decision-maker) of people with dementia in end of life care planning [7]. If health care proxy decision-makers are aware that end of life is approaching, people with advanced dementia are less likely to have invasive interventions in the months prior to death [8]. Lack of prognostic guidance is, however, a common barrier to health care proxy decision-makers engaging in decisions to avoid burdensome interventions such as hospital transfers [9].

There has been limited previous research aimed at identifying indicators of increased mortality risk for people with dementia living in RACFs. The Advanced Dementia Prognostic Tool (ADEPT) was developed to assess prognosis for residents with advanced dementia living in long-term care [10] but external prospective validation only demonstrated modest ability to discriminate for 6-month mortality (c statistic 0.67) [11]. The variables used to develop the ADEPT model were limited to those contained in the long-term care minimum data set (MDS), an administrative data set used throughout the USA for assessment of care quality and allocation of funding [12]. MDS data is not collected for the purpose of identifying indicators of deteriorating health for people with dementia and the accuracy of the clinical information contained within the MDS is variable [13]. Reliance on MDS data limits the clinical utility of the ADEPT model for use outside the US long-term care setting, and it is unknown whether there are clinical variables not collected in the MDS that would better identify people with dementia who are at increased risk of mortality.

In Australia, MDS assessments are not routinely undertaken and the Aged Care Funding Instrument (ACFI) is instead used to determine the level of care and funding [14]. ACFI assessments are infrequently updated following admission to residential care and in a recent cross-sectional analysis, the average time since last ACFI completion was greater than 12 months across RACFs in Australia [15], making these assessments unsuitable for detecting clinical deterioration. Important changes in clinical conditions not captured in ACFI data are recorded during routine clinical care but there is currently no standardized process for identifying and responding to prognostic indicators associated with increased mortality.

## Objectives

This study will aim to develop a prediction model for 6- and 12-month mortality for RACF residents with dementia using prognostic indicators recorded during routine clinical care. The model is intended to be applicable to people with dementia who have been living in a RACF for at least 3 months and to be utilized from 3 months onwards during the RACF admission.

## Methods

### Study design

This is a secondary analysis of a cohort of people with dementia from RACFs participating in a cluster-randomized trial of a simulation-based palliative care education intervention (IMPETUS-D) [16]. The cohort includes people with dementia living in RACFs in three states in Australia (Victoria, South Australia, and New South Wales) administered by a single-aged care provider. Residents do not receive any additional treatment or intervention through the IMPETUS-D program and participation is voluntary for all staff. Ethics approval for the study was obtained from the Melbourne Health Human Research and Ethics Committee (HREC/17/MH/336) as a component of the IMPETUS-D project ethics application. The study protocol has been designed in accordance with the TRIPOD statement for transparent reporting of the development of multivariable predictive models [17]. Prognostic indicator variables are extracted from RACF records retrospectively from the time of IMPETUS-D randomization using the date of most recent weight measurement as *t*0. Mortality will then be assessed prospectively for each resident at 6 and 12 months after *t*0.

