### Data source

Data from RACF files has been accessed by site co-ordinators using a centralized database administered by the aged care provider. This database contains information recorded during routine clinical care and no assessment of residents will be undertaken outside of that required for usual care. Enrolment of participants occurred over a 12-month period during the pre-implementation and training phase of the IMPETUS-D project from December 2018, to December 2019, with baseline data and prognostic indicator variables collected at the time of enrolment. Mortality data will be collected until December 2020 and recorded at 6- and 12-month intervals post-assessment of prognostic indicator variables (*t*0). All study data will be recorded using the Research Electronic Data Capture tool (REDCAP) [18] in a secure online database administered by the University of Melbourne, Australia. The research database can only be accessed by research staff working on the project and all records will be stored for a minimum of 5 years after study completion.

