### Participants

The cohort will comprise a minimum of 900 residents with dementia. Only residents who have been admitted to the RACF for a period of at least 90 days prior to enrolment will be eligible for inclusion if they have a documented diagnosis of dementia based on ICD-10 dementia definitions. Evidence of moderate to severe dementia will be required for study inclusion based on the cognitive skills assessment contained within the Aged Care Funding Instrument (ACFI) and dementia FAST staging.

The ACFI is a mandatory assessment instrument used to determine care needs and funding allocation for all residents of RACFs in Australia. Cognitive skills within the ACFI are divided into four groups (A, B, C, D) based on increasing degree of impairment such that group A has minimal impairment and group D has the most severe level of impairment. People with dementia with cognitive skills classified as group C or D (moderate to severe cognitive impairment) will be eligible for inclusion in the study. ACFI assessment of cognition uses the Psychogeriatric Assessment Scales—Cognitive Impairment Scale (PAS-CIS). This scale has been demonstrated to correlate well with the Mini-Mental State Examination (*r* = −0.77) [19] with higher scores indicating more severe impairment. Those with a PAS-CIS score of 10-15 are classified as cognitive skills C and those with a score of 16 or above as cognitive skills D. If the PAS-CIS score is not complete, the resident will be included if the ACFI appraisal determines that the resident meets the criteria to be classified as cognitive skills C or D based on evidence that they need assistance with the performance of activities of daily living due to cognitive impairment. In addition to ACFI criteria, study participants will need to meet the criteria for FAST stage 6e dementia at study entry. FAST staging correlates well with the trajectory of cognitive decline in moderate to advanced stages of dementia [20, 21] and stage 6e has been chosen as it represents the threshold for transition to the most advanced stage of dementia (FAST stage 7) for whom prognostic information may be particularly clinically relevant.

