### Outcomes

Mortality data will be collected prospectively through a review of RACF files to identify all residents who died during the follow-up period. For any study participants who leave the RACF prior to 12 months of follow-up mortality information will be requested from the Department of Births Deaths and Marriages. Mortality will be divided for analysis into those that occurred within 6 months of study entry and those that occurred within 12 months of study entry. These mortality end points were chosen as they were considered most clinically meaningful. Estimation of the likelihood of death within 6 months is required for hospice eligibility in the USA [24] and is the end point for which the ADEPT model was developed. The Australian Commission on Safety and Quality in Healthcare focuses on those who are “likely to die within the next 12 months” in guidelines regarding end of life care [25] and whether a clinician would be surprised by death within 12 months (“the surprise question”) is often used for end of life identification [26].

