### Candidate predictor variables

The prognostic indicators for consideration in the multivariable model were identified from a literature review (unpublished) examining clinical features associated with increased mortality for people with dementia (see Table 1). Given the aim is to create a model that could be readily incorporated into routine clinical care, a parsimonious approach was taken to a selection of prognostic indicators with ten variables selected that could be easily assessed by RACF staff through a brief audit of the patient record. The number of variables chosen was also informed by consideration of the minimum number of events per variable required for model development (see sample size below).

**Table 1 Tab1:** Candidate predictor variables

At study entry	Prior to study entry
Age [27]	Pressure injuries within the last 3 months [28, 29]
Sex [27]	Weight loss over the last 6 months [30]
Level of support required for oral intake [31]	Infections in the last 3 months [29]
Level of support required to transfer out of bed [31]	Hospital admissions in the last 3 months [32]
BMI [33]	Number of falls in the last 3 months [34]

Pressure injuries, infections, falls, and hospital admissions are recorded through mandatory clinical documentation during routine care at the participating RACF sites. The frequency of these clinical episodes will be assessed for 3 months prior to study entry. More than 10% weight loss in 6 months has been identified as a predictor of mortality in previous studies and thus a 6-month period was chosen for calculation of percentage weight loss [10, 30].

The level of staff assistance for oral intake and transferring out of bed will be assessed from care documented in RACF files and quantified using descriptors from the Minimum Data Set ADL Scale (MDS ADL). The MDS ADL scale has been validated against other functional assessment scales in long-term care [35] and is able to detect change in function for people with cognitive impairment living in RACFs [36]. A decline in MDS ADL scale scores for oral intake and transferring ability, in particular, occurs more commonly in the last months of life for people with advanced dementia [31]. The MDS ADL scale divides the level of assistance required to complete a task into five categories of increasing dependence. A score of zero is given for independence, increasing to a score of four for total dependence on staff to complete the activity.

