The developed model should be considered preliminary and not be incorporated into clinical care without further study. In the current study design, heterogeneity in the duration of time the cohort has been living in long-term care at study entry (*t*0) may introduce survivorship bias. People with dementia newly admitted to long-term care have higher mortality rates within the first 3 months [42, 59] and excluding this group aims to develop a model that only applies to survivors of this high-risk period. To address the issue of survivorship bias, further study is needed involving a cohort followed prospectively from 3 months after RACF admission. Future research combining serial assessment of prognostic indicator variables with dynamic modeling techniques would also allow the model to be utilized across multiple time points. Comparing the performance of the developed model to the ADEPT model in an Australian RACF cohort will also be an important aspect of further validation of the model. The variables required for the ADEPT model are not routinely assessed during clinical care at RACFs in Australia and require additional assessment of residents that is beyond the scope of this model development study.

Even after further validation, there will always be uncertainty with predictive models and the aim is to provide guidance about potential illness trajectory to health care providers rather than replace clinical judgment. It is hoped that, once externally validated, a clinical tool could be developed to enable better identification of residents with dementia at greatest risk of mortality over the following 12 months for whom access to resources such as specialist geriatric medicine and palliative care support may be most critically needed to optimize care and facilitate anticipatory end of life care planning. Future development of a decision support tool would require the involvement of health professionals working in RACFs, people with dementia, and their caregiver’s in order to ensure that mortality risk information is utilized appropriately to meet the needs of the population that the tool intends to support.

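### Follow-up starts at the last weight, but residents join the cohort at enrolment; if they must be alive then, the gap is immortal time and absolute risk is understated

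*Protocol article*

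**What the plan says.** All places are in the protocol article.

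- **Study design** extracts the predictors "retrospectively from the time of IMPETUS-D randomization using the date of most recent weight measurement as" *t*0. It continues: "Mortality will then be assessed prospectively for each resident at 6 and 12 months after" *t*0.
- **Data source** says enrolment ran from December 2018 to December 2019, "with baseline data and prognostic indicator variables collected at the time of enrolment". Deaths are "recorded at 6- and 12-month intervals post-assessment of prognostic indicator variables", and that assessment is labelled *t*0.
- **Participants** admits only residents "admitted to the RACF for a period of at least 90 days prior to enrolment". The residence rule therefore runs to enrolment, not to *t*0.
- **Outcomes** divides deaths into "those that occurred within 6 months of study entry and those that occurred within 12 months of study entry".
- **Candidate predictor variables**, on pressure injuries, infections, falls and hospital admissions: "The frequency of these clinical episodes will be assessed for 3 months prior to study entry".
- **Discussion** treats study entry and *t*0 as one date, in noting that differing time "living in long-term care at study entry (*t*0) may introduce survivorship bias".

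The article does not state how often residents are weighed, how old the last weight may be, how randomization and enrolment dates relate for a resident, or on which date a resident must be alive to be included.

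**The concern.** By its definition *t*0 falls on or before randomization, whereas entry to the cohort is tied to enrolment. If only residents alive at enrolment are included, anyone who died between the last weight and enrolment is absent, and every included resident has survived that interval with certainty. Counting it as follow-up is immortal time: the 6- and 12-month windows each lose part of the period in which a death can be observed.

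Absolute risk is the model's product. Staff would score a living resident from a record audit, and a risk counted from an older weight partly covers time that resident has already survived. The planned bootstrap, calibration curves and leave-center-out validation all use the same clock, so the model could look well calibrated and still understate risk from the date of assessment.

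Two further problems follow from the unreconciled dates:

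- Predictors collected at enrolment could include falls, infections or admissions that happened after *t*0, inside the outcome window.
- A resident with 90 days' residence at enrolment may have fewer at *t*0. Follow-up would then begin in the early high-mortality period that the Discussion says is excluded.

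**Working it through.** **Inputs.** From Sample size: 12-month mortality of about 30%, at least 200 deaths required, cohort of at least 900. Assumed here: a constant hazard, inclusion conditional on being alive at enrolment, enrolment on or after *t*0, and the length of the gap *g* from *t*0 to enrolment.

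**The plan's own figures.** 200 / 0.30 = 666.7, so 667, as stated. The shrinkage criterion gives 10 / [(0.9 − 1) × ln(1 − 0.208/0.9)] = 380.5, so 381, with 381 × 0.3 / 10 = 11.43 events per variable, also as stated. The sample size arithmetic is sound.

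**Risk with no gap.** λ = −ln(0.70)/12 = 0.0297 per month. The 12-month risk is 30.0%. The 6-month risk is 1 − exp(−6λ) = 16.33%; this is derived and does not appear in the article.

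**Risk counted from *t*0 among residents alive at enrolment.** For a horizon of *H* months and a fixed gap *g*:

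risk = 1 − exp[−λ(*H* − *g*)]

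For gaps spread evenly from 0 to *m* months, this is averaged over *g*:

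risk = 1 − exp(−λ*H*) × [exp(λ*m*) − 1] / (λ*m*)

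*Mean gap 0.5 month:*
- 12 months: 1 − exp(−0.0297 × 11.5) = 28.95%, which is 1.05 points or 3.5% (relative) too low.
- 6 months: 1 − exp(−0.0297 × 5.5) = 15.08%, which is 1.25 points or 7.7% too low.
- An even spread over 0 to 1 month gives the same risks to two decimals.

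*Mean gap 1.5 months (even spread over 0 to 3 months):* the bracketed factor is 1.0459.
- 12 months: 1 − 0.7000 × 1.0459 = 26.78%, which is 3.22 points or 10.7% too low.
- 6 months: 1 − 0.8367 × 1.0459 = 12.49%, which is 3.84 points or 23.5% too low.

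*No gap:* no bias.

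**Simulation.** Two million exponential survival times, keeping only those surviving the gap, gave 29.0% and 15.1% for gaps of 0 to 1 month, and 26.8% and 12.6% for gaps of 0 to 3 months (12- and 6-month risks respectively).

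**Effect on event numbers.** At 900 residents and a 0.5-month gap, 900 × 0.2895 ≈ 261 deaths are expected by 12 months instead of 270, still above 200.

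**The case against.** **One outcome clock.** A reader might infer that the outcome has two clocks, because Study design and Data source use *t*0 while Outcomes and Candidate predictor variables use study entry. The document does not support that: the Discussion writes study entry and *t*0 as the same date. The second clock is enrolment/randomization. It follows that the 3-month look-back windows, timed from study entry, nominally end at *t*0, and that collection at enrolment may mean only when the records were abstracted. Events after *t*0 entering as predictors is therefore a possibility the text leaves open, not something it prescribes.

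**Survival to enrolment is not written.** Extraction is retrospective from a central database, so residents who died in the gap could in principle have been kept. This stands, and it makes the bias conditional. Exclusion is still the natural reading, because the cohort is described as people living in the facilities and eligibility is set at enrolment.

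**The size may be small.** With recent weights the shift is about 1 point, comparable with simple binomial standard errors at 900 residents: √(0.30 × 0.70/900) = 1.5 points and √(0.163 × 0.837/900) = 1.2 points. That is fair, but the bias is systematic and does not shrink with more residents.

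**The weight date has a purpose.** It aligns BMI and weight loss, two of the ten predictors, with the start of follow-up. This is a real advantage. It can largely be kept by limiting the age of the weight.

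**The model is preliminary.** The Discussion says so, and external validation is required before clinical use. That limits the immediate harm. It does not justify building the model on a clock that its internal checks cannot test.

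**Conclusion.** The concern holds in conditional form. The article starts follow-up at the last weight but enrols residents and applies eligibility at enrolment, without reconciling the dates. If residents must be alive at enrolment, absolute risk is understated whenever the gap is positive. The shortfall is about 1 point at each horizon for a mean gap of 0.5 month. For a mean gap of 1.5 months it is about 3.2 points at 12 months and 3.8 points at 6 months. These figures rest on a constant hazard, the article's 30% mortality and gap lengths the article does not give.

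Three stronger readings are not supported:

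- **Certain downward bias.** Survival to enrolment is implied only, and the gap could be close to zero.
- **Distorted coefficients.** A reader might suppose that the sickest residents have the oldest weights, so that frailty effects are biased too. That is plausible, but nothing in the article documents it.
- **Too few events.** About 261 deaths are still expected at a 0.5-month gap, so the 200-event target is not threatened.

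The survivorship bias conceded in the Discussion concerns time since admission and does not cover this gap.

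**What to change.** Define one index date for every resident: the enrolment or record-audit date. Require residents to be alive and to meet all eligibility criteria, including the 90 days' residence, on that date. Start both mortality clocks and end all look-back windows there. Use the last weight within a prespecified maximum age for BMI and weight loss; if there is none, treat it as missing under the planned MICE.

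If *t*0 must stay at the weight date, there are two fallbacks:

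- include every resident alive and eligible at *t*0, whether or not they survived to enrolment; or
- report the distribution of the *t*0-to-enrolment gap and repeat the model with the clock started at enrolment.

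The cost is revised wording, recalculation of the outcomes and a few more missing weights. If only event counts were kept, and not event dates, moving the end of the look-back windows could require re-extraction. Enrolment ended in December 2019 and mortality collection runs to December 2020, so 12 months from the last enrolment is still covered at month resolution, though with little margin.
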